### Outcome assessment

The primary outcome measure to assess efficacy of Oncokompas is patient activation. Secondary outcome measures include self-efficacy, personal control, perceived patient-physician interaction, mental adjustment to cancer, need for supportive care and HRQOL. Furthermore, cost-utility outcomes will be assessed. *Reach* is defined as the percentage of cancer survivors who get access to Oncokompas within the context of this RCT. To obtain insight into possible factors associated with reach, we will obtain data on socio-demographic and clinical characteristics, health literacy, health locus of control (HLC), Internet use, attitude towards eHealth and the outcome measures on efficacy.

Primary and secondary outcome measures to measure efficacy are collected at baseline, post-intervention and at 3- and 6-month follow-up. Cost-utility outcomes are collected at baseline and at 3- and 6-month follow-up. Outcome measures to investigate associations of reach are collected at baseline. An overview of the outcome measures is presented in Table 1.

**Table 1 Tab1:** Study outcome measures and instruments

Outcome measure	Instrument
Efficacy^a^	
Primary outcome measure	
Patient activation	Patient Activation Measure (PAM)
Secondary outcome measures	
Self-efficacy	General Self-Efficacy Scale (GSE)
Personal control	Pearlin Mastery Scale (PMS)
Perceived patient-physician interaction	Five-item Perceived Efficacy in Patient-Physician Interactions (PEPPI-5)
Need for supportive care	34-item Short Form Supportive Care Needs Survey (SCNS-SF34) and head and neck cancer-specific module (SCNS-HNC)
Mental adjustment to cancer	Mental Adjustment to Cancer Scale (MAC)
Health-related quality of life	EORTC QLQ-C30
	EORTC QLQ-BR23
	EORTC QLQ-CR29
	EORTC QLQ-H&N43
	EORTC QLQ-HL27
	EORTC QLQ-NHL-LG20
	EORTC QLQ-NHL-HG29
Cost-utility measures^b^	
Outcome measures on cost-utility	
Quality-adjusted life-years	5 dimension EuroQol questionnaire (EQ-5D)
Medical costs	iMTA Medical Consumption Questionnaire (iMCQ)
Productivity costs	iMTA Productivity Cost Questionnaire (iPCQ)
Reach^c^	
Associations of reach	
Health literacy	Functional, Communicative and Critical Health Literacy scales (FCCHL)
Health locus of control	Multidimensional Health Locus of Control (MHLC)
Internet use	Adapted version of van de Poll-Franse and Van Eenbergen questionnaire [44]
Attitude towards eHealth	e-Health Impact Questionnaire (eHIQ)
Socio-demographic and clinical characteristics	Study-specific questionnaire

*Abbreviations: EORTC QLQ-C30/BR23/CR29/H&N43/HL27/NHL-HG29/NHL-LG20* 30-item core European Organisation for Research and Treatment of Cancer Quality of Life Questionnaire /breast cancer, 23 items/colorectal cancer, 29 items/head and neck cancer, 43 items/Hodgkin lymphoma, 27 items/non-Hodgkin lymphoma, high grade, 29 items/non-Hodgkin lymphoma, low grade, 20 items; *iMTA* Institute for Medical Technology Assessment

^a^Assessment at T0, T1, T2 and T3

^b^Assessment at T0, T2 and T3

^c^Assessment at T0

#### Efficacy

##### Primary outcome measure: patient activation

The Patient Activation Measure is a 13-item PROM on self-reported knowledge, skills and confidence in self-management of one’s health or chronic condition. Patients are asked to report their level of agreement with various statements on a 4-point Likert scale (i.e., strongly disagree, disagree, agree, strongly agree) or to indicate that the item is not applicable. A total score can be calculated by calculating a mean score of all the applicable items (items which were answered on the 4-point scale), which is transformed to a standardised activation score ranging from 0 to 100 [21].

##### Secondary outcome measures

*Self-efficacy*

The General Self-Efficacy Scale (GSE) is designed to assess optimistic self-beliefs regarding coping with a variety of difficult demands in life. The GSE consists of ten items scored on a 4-point Likert scale ranging from 1 (not at all true) to 4 (exactly true). The scores of the ten items are summed to give a total score. A higher score reflects a higher generalised sense of self-efficacy [22].

*Personal control*

The Pearlin Mastery Scale (PMS) measures global sense of personal control. It consists of seven items, and individuals respond to a 5-point Likert scale about the extent to which they agree (5 = strongly agree) or disagree (1 = strongly disagree) with the various statements. A PMS score ranges from 7 to 35, with a higher score reflecting greater mastery [23].

*Perceived patient-physician interaction*

The five-item Perceived Efficacy in Patient-Physician Interactions measures patients’ confidence in interacting with their main care provider using the short five-item version of the scale. Patients can indicate on a 5-point Likert scale (1 = not at all confident to 5 = completely confident) how confident they are that they, for example, know which questions to ask or are able to make the most out of their care provider visit [24, 25].

*Need for supportive care*

The 34-item Short Form Supportive Care Needs Survey (SCNS-SF34) measures the need and level of need for supportive care in the last month on the basis of 34 items using a 5-point, two-level response scale. The first response scale consists of two broad categories of need: ‘no need’ and ‘a need’. The ‘no need’ scale is further subdivided into ‘not applicable’ for issues that are not a problem to the patient and ‘satisfied’ for issues on which a patient needs support but the support is satisfactory. The ‘need’ category has three subcategories indicating the level of need for additional care: ‘low need’, ‘moderate need’ and ‘high need’ [26, 27].

In conjunction with SCNS-SF34, a tumour-specific module for patients with head and neck cancer can be used. The SCNS-HNC measures the need for supportive care concerning 11 HNC-specific issues using the same response scale as the SCNS-SF34 [28].

*Mental adjustment to cancer*

Cognitive and behavioural responses to cancer diagnosis and treatment are determined using the Mental Adjustment to Cancer scale (MAC). The MAC comprises five subscales: Fighting Spirit, Helplessness/Hopelessness, Anxious Preoccupation, Fatalism and Avoidance. The 40 items are rated on a 4-point Likert scale ranging from 1 for ‘definitely does not apply to me’ to 4 for ‘definitely applies to me’. A higher score represents a higher endorsement of the adjustment response [29].

*Health-related quality of life*

The 30-item core European Organisation for Research and Treatment of Cancer Quality of Life Questionnaire (EORTC QLQ-C30) is a cancer-specific quality-of-life questionnaire developed for repeated assessments within clinical trials. It was developed in a cross-cultural setting and is a valid and reliable instrument for quality-of-life assessments in various cancer populations. It contains five functional scales (physical, cognitive, emotional, social and role), a global quality-of-life scale, three symptom scales (pain, fatigue and nausea/vomiting) and six single items (dyspnoea, insomnia, loss of appetite, constipation, diarrhoea and financial difficulties). All scales and single items range in score from 0 to 100. A higher score on one of the functioning scales or the global quality-of-life scale represents a better quality of life, whereas a higher score on the symptom scales or the single items indicates a higher level of symptoms [30, 31].

In conjunction with the EORTC QLQ-C30, tumour-specific modules can be used. EORTC QLQ-BR23 is a module meant to be used among patients with breast cancer, varying in stage of disease and treatment. It consists of four functional scales (body image, sexual functioning, sexual enjoyment and future perspective), three symptom scales (systemic therapy side effects, breast symptoms and arm symptoms) and one symptom item (distress caused by hair loss) [32].

EORTC QLQ-CR29 is a module meant to be used among patients with colorectal cancer. It includes two functional scales (body image and future health perspective) and five symptom scales (micturition problems, gastrointestinal problems, defecation problems, sexual problems and chemotherapy-related problems) [33].

EORTC QLQ-H&N43 is a module meant to be used among patients with head and neck cancer. It contains 13 symptom scales (pain, swallowing, senses, speech, social eating, social contact, physical contact, skin, shoulder, body image, teeth, dry mouth and sticky saliva, and anxiety) and 6 symptom items (trismus, cough, lymphedema, wound healing, neurological problems and weight) [34].

EORTC QLQ-HL27, EORTC QLQ-NHL-LG20 and EORTC-QLQ-NHL-HG29 are modules meant to be used with patients with Hodgkin’s lymphoma, low-grade non-Hodgkin’s lymphoma and high-grade non-Hodgkin’s lymphoma, respectively. All modules have four multi-item scales, but they differ in the number of items per scale: symptom burden due to disease and/or treatment (4–7 items), physical condition/fatigue (4 or 5 items), emotional impact (4–6 items), and worries/fears health and functioning (8–11 items), with an extra item scale on neuropathy (2 items) for EORTC QLQ-NHL-HG29. For all scales, a higher score reflects worse or more symptoms/problems.

#### Outcome measures on cost-utility

A cost-utility analysis will be conducted; that is, the difference in total 6-month costs between the two arms will be compared with the difference in quality-adjusted life-years (QALYs) based on the 5-dimension EuroQol questionnaire (EQ-5D). The EQ-5D consists of five items measuring problems in five dimensions of quality of life (mobility, self-care, usual activities, pain/discomfort and anxiety/depression). Patients can answer that they have no problems, some problems or extreme problems [35]. The resulting profile of answers (1 of 243 possibilities) can be transformed to a value given by the general public: the EQ-5D index using the Dutch index tariff [36]. Furthermore, a visual analogue scale is included, which represents the patient’s judgment of his or her own health state on a scale from 0 (worst health state) to 100 (best health state).

Direct medical costs (healthcare and medication use), direct non-medical costs (travelling costs and help received from family or friends) and indirect non-medical costs (productivity losses) in the previous 3 months will be measured using an adapted version of the Institute for Medical Technology Assessment Medical Consumption Questionnaire (iMCQ) [37] and Institute for Medical Technology Assessment Productivity Cost Questionnaire (iPCQ) [38] of the Institute for Medical Technology Assessment (iMTA) of Erasmus University Rotterdam (Rotterdam, The Netherlands). In addition, a case report form on healthcare use in the hospital during the study period, including medical specialist visits, day treatment and hospital admission, will be completed using the hospital information system.

#### Reach

*Reach* is defined as the percentage of cancer survivors who get access to Oncokompas within the context of this RCT. More precisely, reach is the percentage of cancer survivors who are willing to participate in the second part of the study and thereby get access to Oncokompas (directly or after 6 months). For the numerator, cancer survivors who are willing to participate in the second part of the study and give their informed consent will be counted. For the denominator, all eligible cancer survivors who are invited to participate in the first part of the study will be counted.

Participants who complete the baseline questionnaire will be asked to participate in the follow-up study. To obtain insight into reasons for non-participation, participants not interested in the follow-up study will be asked to indicate their reasons for non-participation in the second part of the study (e.g., no interest in scientific research or no interest in the eHealth self-management application Oncokompas) by means of multiple-choice questions.

##### Associations of reach

To obtain insight into possible factors associated with reach, we will obtain data on socio-demographic and clinical characteristics, health literacy, HLC, Internet use, attitude towards eHealth, and the outcome measures on efficacy.

##### Socio-demographic and clinical characteristics

A study-specific questionnaire comprises questions about socio-demographics (age, marital status, family situation, education level) and clinical characteristics (co-morbidities). Clinical characteristics, including information on cancer type (breast, colorectal, head and neck cancer or lymphoma), cancer stage (TNM classification), cancer treatment and time since diagnosis, will be extracted from the NCR.

##### Health literacy

The validated Dutch translation of the self-report Functional, Communicative and Critical Health Literacy scales will be used to measure health literacy. The 14-item questionnaire asks for information on how often patients have had problems with health information and the extent to which they extracted, communicated and analysed health information. The answers are scored on a 4-point Likert scale ranging from 1 = ‘never’ to 4 = ‘often’ for functional health literacy and 1 = ‘easy’ to 4 = ‘rather difficult’ for communicative and critical health literacy [39, 40].

##### Health locus of control

HLC is measured with the Multidimensional Health Locus of Control (MHLC) scale form B. The MHLC scale comprises 18 diagnostic statements describing three dimensions of HLC: internal, powerful others and chance. The subscales ‘powerful others’ and ‘chance’ represent external HLC. People with high external HLC scores are presumed to have generalised expectancies that factors such as fate, luck, chance or powerful others will determine their health outcomes, whilst people with high internal HLC scores are presumed to hold the belief that someone becomes healthy or unwell as a result of their own behaviour. Each of the three subscales contains six items measured on a 6-point Likert scale ranging from 1 = ‘strongly disagree’ to 6 = ‘strongly agree’. The scores of each subscale range from 6 to 36 points; the higher the score, the stronger the self-perceived influence of a given factor [41–43].

##### Internet use

Internet use will be measured with an adapted version of the questionnaire developed by van de Poll-Franse and van Eenbergen [44]. It comprises three broad applications of Internet use (content, communication and community), of which only the application of ‘content’ will be used in this study, with ten multiple-choice items about the content of Internet use and content of Internet searches.

##### Attitude towards eHealth

General attitudes towards using the Internet to access health information will be measured using part 1 of the e-Health Impact Questionnaire, which consists of two subscales: attitudes towards online health information (five items) and attitudes towards sharing health experiences online (six items). All items have a 5-point response category ranging from ‘strongly disagree’ to ‘strongly agree’. Each scale will be transformed to a 0–100 metric, where 0 represents a low perceived value and 100 a high perceived benefit of using the Internet in relation to health [45].

### Sample size

To demonstrate presence of an effect between T3 and T0 of at least 0.5 standard units as statistically significant in a one-tailed test at α = 0.05 and a power of (1 − β) = 0.80, a minimum of 51 participants per arm in each condition will be required at follow-up. Anticipating a drop-out rate of 25% between T0 and T3, 68 participants per condition arm per tumour type need to be included at T0. The total study cohort thus comprises 544 cancer survivors representing 136 cancer survivors per tumour type (breast, colorectal, and head and neck cancer or lymphoma).

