### Randomisation

Cancer survivors who meet the inclusion criteria and give informed consent for the second part of the study are randomly allocated in a 1:1 ratio to either the intervention group (access to Oncokompas) or the wait-list control group (access to Oncokompas after a 6-month waiting period). Randomisation to either the intervention or the control group will be performed by a researcher not involved in the study using block randomisation. The blocks will have a length of 68. The researcher will determine all possible balanced combinations of assignment within the block (i.e., equal number for all groups within the block). Randomisation will be stratified by tumour type (breast, colorectal, and head and neck cancer or lymphoma). It is expected that this variable has prognostic relevance and therefore needs to be distributed evenly across both groups. The allocation sequence will be generated by PROFILES and will be made available by a data download from the PROFILES database. The researcher ([name]) will assign participants either to the intervention group and invite participants to engage with Oncokompas by email or to the control group and place participants on the waiting list, where the participants’ email address is blocked from Oncokompas for 6 months.

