### Statistical analyses

Descriptive statistics will be generated for all socio-demographic and clinical characteristics and outcome measures. Chi-square tests, independent samples *t* tests (in case of normality of the measure) and Mann-Whitney *U* tests (in case of non-normality of the measure) will be used to analyse whether randomisation resulted in comparable patient groups. A *p* value of <0.05 will be considered significant. Analyses will be performed using IBM SPSS Statistics version 22 (IBM, Armonk, NY, USA) and Stata version 12.1 (StataCorp, College Station, TX, USA) software.

To investigate the efficacy of Oncokompas, linear mixed-effect models will be used to compare longitudinal changes in outcome measures for efficacy in both groups over time (intention-to-treat analyses). Independent samples *t* tests will be used to measure differences between the intervention and control groups at follow-up assessments. Cohen’s *d* [46] will be calculated as a measure of effect size (ES) for intervention group versus control group. Cohen’s *d* is computed as the difference between two means, divided by the pooled SD. The magnitude of the ES is classified as large (≥0.80), moderate (0.50–0.79) or small (<0.50) [47].

To investigate associations of the reach of Oncokompas within this RCT, chi-square tests, independent samples *t* tests and Mann-Whitney *U* tests will be used to analyse whether there are differences between participants and non-participants in the follow-up study (part 2) regarding baseline characteristics (part 1).

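### The stated 80% power belongs to a one-tailed comparison within each tumour type, while the efficacy analyses described compare the two arms overall

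*Protocol article*

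**What the plan says.** In the Sample size section, the target is "an effect between T3 and T0 of at least 0.5 standard units", to be found "statistically significant in a one-tailed test at α = 0.05 and a power of (1 − β) = 0.80". The section concludes that "a minimum of 51 participants per arm in each condition will be required at follow-up". It continues with "Anticipating a drop-out rate of 25% between T0 and T3" and arrives at "68 participants per condition arm per tumour type need to be included at T0", hence 136 per tumour type and 544 in all.

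The Randomisation section stratifies by tumour type and gives the reason: "It is expected that this variable has prognostic relevance and therefore needs to be distributed evenly across both groups".

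The Statistical analyses section uses linear mixed-effect models to "compare longitudinal changes in outcome measures for efficacy in both groups over time", followed by independent-samples t tests between the two arms at the follow-up assessments and Cohen's d for one arm against the other. Significance is p < 0.05, with sidedness not given. Tumour type does not appear in the efficacy part of that section. The Discussion announces secondary moderator analyses to learn which subgroups benefit most, without naming the moderators.

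**The concern.** One two-arm comparison under the stated assumptions needs 2 × 68 = 136 participants. The remaining 544 − 136 = 408 are there because the requirement is repeated for each tumour type. That multiplication makes sense if a conclusion is wanted in each type, but the analysis section describes one comparison across all types.

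A reader therefore cannot tell whether success means an overall effect or an effect in each type. The two differ widely in power and in the size of effect that can reach significance. If this stays open, the choice between an overall and a type-specific claim could be made after the results are known. The power statement also gives no guide to what the overall test can detect, which is an effect well below the 0.5 SD used for sizing.

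**Working it through.** **Inputs (Sample size section).** Effect 0.5 SD; α = 0.05, one-tailed; power 0.80; 51 completers per arm; 25% drop-out; four tumour types. I read 0.5 SD as a standardised difference between arms. A within-person reading would give (1.645 + 0.842)² / 0.5² = 24.7, which does not match 51.

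**Reproducing the plan's figures.**
- Normal approximation: n per arm = 2 × (1.645 + 0.842)² / 0.5² = 49.5, so 50. The t-based solution is 50.15, so 51.
- Drop-out: 51 / 0.75 = 68.
- Total: 68 × 2 arms × 4 types = 544.
- A two-sided test would need 63 per arm (t-based 63.8, so 64) and does not match.

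So 51, 68, 136 and 544 are reproduced as a one-tailed comparison inside each tumour type.

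**Power of that comparison (51 per arm, 0.5 SD).** The standardised distance is 0.5 × √(51/2) = 2.525.
- One-tailed: Φ(2.525 − 1.645) = 0.81 (t-based 0.806).
- Two-sided: Φ(2.525 − 1.960) = 0.71 (t-based 0.706).

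**Power of the overall comparison.** Completers per arm: 4 × 51 = 204. The distance is 0.5 × √(204/2) = 5.050.
- One-tailed: Φ(5.050 − 1.645) = 0.9997.
- Two-sided: Φ(5.050 − 1.960) = 0.999.

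**Effect detectable overall with 80% power.** √(2/204) = 0.0990.
- One-tailed: (1.645 + 0.842) × 0.0990 = 0.25 SD.
- Two-sided: (1.960 + 0.842) × 0.0990 = 0.28 SD.

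On the effect-size scale in the Statistical analyses section, 0.28 falls in the small class (below 0.50), whereas the sizing effect of 0.5 sits at the lower edge of moderate.

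**Adjustment for the stratum (assumption).** The documents do not say how much outcome variance tumour type explains. For a t test at one time point, leaving out a factor that explains a share R² inflates the standard error by 1/√(1 − R²): 1.026 at an assumed 5% and 1.054 at an assumed 10%. For a true effect of 0.25 SD with 204 per arm, two-sided power would go from 71.4% unadjusted to 73.6% or 75.9% adjusted. In a mixed model of change the gain would be smaller, because a constant difference between tumour types largely drops out of a group-by-time contrast.

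**The case against.** The strongest reply is that a journal article condenses the analysis. The Statistical analyses section lists no covariates or random effects, so its silence on tumour type does not show that the model leaves it out. That stands. A reader might infer that the mixed model ignores the stratum and so has inflated standard errors, but the article does not establish this. It does, however, name independent-samples t tests for the follow-up comparisons, and those make no allowance for the stratum.

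Other strong inferences also fail:
- **That no analysis will examine tumour type.** The Discussion plans moderator analyses, and tumour type may be among them. But a moderator test is an interaction, which is not the within-type comparison that was powered.
- **That the trial was sized by type because type is prognostic.** That reason is given for stratifying randomisation only; the Sample size section gives none.
- **That the mismatch leaves the trial short of power.** The opposite is true for the overall comparison at 0.5 SD.
- **That the plan carries an inflated false-positive risk from four tests.** Four unadjusted tests at 5% would give 1 − 0.95⁴ = 18.5% if independent, but the article does not say that four such tests will be run.

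What the reply does not remove is the mismatch between two things the article states: a sample size built within tumour type and efficacy comparisons made across types.

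**Conclusion.** The point holds as a mismatch between the sample-size statement and the analyses described. The 80% figure describes a one-tailed test within one tumour type (81% by recalculation, 71% if two-sided). The overall comparison that the article does describe has about 99.9% two-sided power at 0.5 SD and can detect about 0.28 SD with 80% power.

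These figures assume 25% drop-out spread evenly over arms and types, and treat the T3 contrast as a comparison of two independent means. The harm is an unclear target of inference and a power figure attached to the wrong test. Any loss of precision from the unadjusted t tests is secondary, and its size cannot be fixed from the documents.

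**What to change.** 1. State that the primary conclusion is the pooled intervention-versus-control contrast in patient activation at T3, and give its sidedness.
2. Rewrite the Sample size section to report two separate powers: pooled (204 per arm) and per tumour type (51 per arm), each with the chosen sidedness.
3. Include tumour type, as the randomisation stratum with four levels, as a fixed effect in the efficacy models. Take the differences at the follow-up assessments from those models instead of from unadjusted t tests.
4. Label tumour-type-specific effects (arm by tumour type) as prespecified secondary analyses, so that they are separate from the unnamed moderators in the Discussion.

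**Cost.** Wording, plus some model degrees of freedom, and no extra participants. The tumour-type main effect takes three. If the secondary analysis is fitted as a full arm × time × type model with four categorical time points, the total rises to as many as 3 + 3 + 9 + 9 = 24, which is affordable with 544 participants.
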